### 2.3.7 Pilot study

The pilot study will be conducted among coaches and medical personnel of the football academies that do not have teams that will participate in the main study. The pilot study will provide the opportunity to assess the use of the data collection forms, measurements and the

questionnaire. A meeting will be held with the participants to discuss about the instruments. The changes will be used to design more appropriate instruments.

### **2.3.8 Data management**

After obtaining the list of all the players from the FERWAFA, they will be assigned codes that will be used to identify them for confidentiality. Collected forms will be kept in a locked and secure drawer in the researchers' office. Moreover, forms will be scanned to keep the soft copies of the collected data that will be saved on a password protected computer and external hard drive for back up.

### **2.3.9 Statistical analysis**

All data will be analyzed statistically using STATISTICA version 12. Standard descriptive statistics will be used for numerical variables as means, standard deviations (SD) or 95% confidence intervals (CI).

In this study incidence for all injuries will be expressed as injuries per 1000 soccer playing hours for the purpose of the comparison with previous epidemiological studies. Risk per 1000 hours of exposure either per match, training or both will be equal to number of injuries multiplied by 1000 per total exposure time. The variations of injuries during match, training or both for the two seasons will be analyzed using Analysis of Variance (ANOVA). ANOVA will also be used to analyze the occurrence of injuries according to the position in the team and division of play. The categorical variables such as the frequency, type, location, severity as well as the mechanism of injuries will be analyzed using a Chi-square test or Fisher's exact test for small numbers. Between groups incidence of injuries will be compared using z-statistics and rate ratios (RR) with a 95% CI will used to present data. The level of significance for all the tests is set to 0.05. Univariate and multivariate regression analyses will be used to calculate odds ratios (ORs) and 95% confidence intervals (CIs) for  $\pm 1$  standard deviation of change. The details of all the statistical analysis that will be performed are provided in the appendix J.

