### **2.3.4 Participants**

The Federation of Rwandese Football Association (FERWAFA) organizes tournaments at different levels. The top flight male first division is composed of 14 teams while 19 clubs compete in the second division.

The first division competition is the country's primary soccer competition. There are 14 men's association soccer clubs that participate in the league and it operate on the process of promotion and relegation. The teams play 26 matches, where each club plays the others twice, during the season which runs from September to June. The total number of matches is 364 matches. The league is currently sponsored by the largest brewer and soft beverage company in Rwanda on its band new beer named "turbo king" and thus officially known as "turbo king national football league". At the end of the completion, the teams are ranked according to the total points accumulated during the season. In case of equal number of points the goal calculation of the number of goals scored and conceded come in favor of the team to determine the winner. The

league winner qualifies to represent the country in the CAF champions' league while the two lowest placed teams are relegated into the second division. Many teams in the first division are sponsored either by private business companies or government institutions (for example, the police, the army and other governmental parastatals) (FERWAFA, 2008).

There are 19 teams competing in the second division organized by the FERWAFA. Unlike the first division, the second division teams do not play each other because each team would play 36 games. Playing many games require many resources from the teams, the organizing federation as well as a longer period of time. Therefore the teams are randomly divided into two groups. Group A composed of 10 teams and group B composed of 9 teams. Teams in each group play each other and accumulate the points according to the win or draw rules. The first two teams in each group qualify to the semifinal stage where they play the teams from the other group. The winners of the semifinal stage qualify to the final and are automatically promoted to the first division. The competition ends while the teams play between 11 and 12 matches. The second division season runs from November to May. The FERWAFA requires each team to register maximum 30 players; therefore the maximum number of players that will participate in this study are 990.

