#### **2.4.8 Statistical analysis**

Analysis of the incidence of injuries comparing the two study groups and the two divisions will be done as explained in the study one. Demographic characteristics of the coaches and responses on the knowledge, perception, readiness and decision making assessment will be analysed using descriptive statistics (range, mean, standard deviation). Categorical data like the coaches’ level of education, highest level of coaching license, availability of the medical personnel into the team will be presented as frequency and percentages. The five injury prevention readiness to practice questions will be coded from zero to five. The minimum score will be zero and the maximum score will be 25. The responses from the perception questions that are on a 5-point Likert scale will be recorded on a range from 1=“very unlikely” to 5=“very likely”. Therefore the results will be analysed using the descriptive statistics with means and standard deviation. Pearson correlation will be used to assess the relationship between perception variable and coaches’ readiness of sports injury prevention. The same test will be used to assess the association between readiness, perception, and first aid knowledge and compliance with the injury prevention programme. Analysis of variance test (ANOVA) will be used to analyse the difference between the coaches’ perceptions, knowledge, and readiness regarding injury prevention in the first division and the second division. The level of significance for all the tests

is set to 0.05. The details of all the statistical analysis that will be performed are provided in the appendix J.

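### The between-group injury rate ratio does not say which rate it compares and has no adjustment for session type; on pooled hours the division contrast can depart from 1 with identical match and training risks

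*Combined protocol and SAP*

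**What the plan says.** Section 2.3.9 states that "incidence for all injuries will be expressed as injuries per 1000 soccer playing hours", and gives comparison with earlier epidemiological studies as the purpose. It then defines risk per 1000 hours, which "either per match, training or both will be equal to number of injuries multiplied by 1000 per total exposure time". So three rates are foreseen: match, training and combined.

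The comparisons in the same section are these:

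- Seasons: "The variations of injuries during match, training or both for the two seasons will be analyzed using Analysis of Variance".
- Playing position and division: "ANOVA will also be used to analyze the occurrence of injuries according to the position in the team and division of play".
- Groups in general: "Between groups incidence of injuries will be compared using z-statistics and rate ratios (RR) with a 95% CI".

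Only the season sentence mentions session type. The regression described in 2.3.9 yields odds ratios per standard deviation, with no exposure offset and no match/training term. For Study Two, 2.4.8 says: "Analysis of the incidence of injuries comparing the two study groups and the two divisions will be done as explained in the study one".

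On match load, 2.3.4 says of the first division: "The teams play 26 matches, where each club plays the others twice, during the season which runs from September to June". Of the second it says: "The competition ends while the teams play between 11 and 12 matches. The second division season runs from November to May". Both statistical sections refer to Appendix J for details; it was not part of the text available for this review.

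**The concern.** An hour of match play and an hour of training need not carry the same injury risk. A combined rate is a weighted average of the two, with each group's own share of match hours as the weight. Dividing by total hours corrects for how much a group plays and trains, but not for the mix. If two groups differ in mix, their combined rates differ even when every match hour and every training hour is equally risky in both.

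The divisions are the groups for which the protocol's own figures show different match loads. What is at stake is the reading of the first-versus-second-division incidence contrast: a difference in fixture lists could be reported as a difference in injury risk, with a significant p-value attached.

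**Working it through.** **Schedule.** Fourteen teams meeting twice play 2 × 13 = 26 matches each, which reproduces the figure in 2.3.4. Over September to June (10 months) that is 2.60 a month. In the second division, 11 to 12 matches over November to May (7 months) is 1.57 to 1.71 a month. The load ratio is 1.52 to 1.65, or 2.60 / 1.643 = 1.58 at 11.5 matches. If the groups of 10 and 9 teams play a single round (an assumption), teams that do not reach the semifinals play only 9 or 8 matches, and the load ratio is 2.02 to 2.28.

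**Assumptions.** The documents give no injury rates and no training volumes. I assume:

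- 11 players × 1.5 h = 16.5 player-hours per match;
- 3 to 5 training sessions of 1.5 h a week, that is 19.5 to 32.5 h per player per month, equal in both divisions;
- 20 to 30 players per squad (2.3.4 sets a maximum of 30);
- a training rate of 2 to 4 per 1000 h;
- a match rate *k* times the training rate, with *k* from 1 to 10;
- the same match rate and the same training rate in both divisions;
- independent Poisson injuries.

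**Formula.** With match share of hours *s*, the pooled ratio (first to second) is [1 + (k − 1)s₁] / [1 + (k − 1)s₂].

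**One case in full** (squad 30, three sessions a week, *k* = 5, training rate 2 per 1000 h):

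- Training hours per team-month: 30 × 19.5 = 585 in both divisions.
- Match hours per team-month: 2.60 × 16.5 = 42.9 and 1.643 × 16.5 = 27.1.
- Match shares: 42.9 / 627.9 = 0.068 and 27.1 / 612.1 = 0.044.
- Pooled ratio: (1 + 4 × 0.0683) / (1 + 4 × 0.0443) = 1.273 / 1.177 = 1.082.
- First-division season hours: 14 × 26 × 16.5 = 6,006 match and 14 × 10 × 585 = 81,900 training. Expected injuries: 6,006 × 0.010 + 81,900 × 0.002 = 224.
- Second-division season hours: 19 × 11.5 × 16.5 = 3,605 match and 19 × 7 × 585 = 77,805 training. Expected injuries: 3,605 × 0.010 + 77,805 × 0.002 = 192.
- z = ln(1.082) / √(1/224 + 1/192) = 0.80, so a two-sided 5% test rejects with probability about 12.5%.

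**Range over the assumptions:**

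| Match rate ÷ training rate | Pooled ratio, 11.5 matches | Pooled ratio, 8 matches | One-season rejection, 11.5 matches |
|---|---|---|---|
| 1 | 1.00 | 1.00 | 5% |
| 3 | 1.03–1.06 | 1.05–1.10 | 6–10% |
| 5 | 1.05–1.11 | 1.09–1.18 | 10–25% |
| 10 | 1.11–1.19 | 1.18–1.34 | 29–70% |

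**Unequal training hours.** The bias follows match share, not matches per month. In the case above, if the first division trains 1.25 times as much the ratio is 1.04; at 1.58 times it is 1.00; at 2 times 0.97; at 2.5 times 0.95.

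**Arms.** Both arms play in the second division. Even if the arms happened to coincide with the 10- and 9-team groups (9 against 8 matches), the pooled ratio is only 1.01 to 1.04 for *k* from 3 to 10.

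**Stratified estimate.** In the worked case the Mantel-Haenszel numerator terms are 60.06 × 3,605 / 9,611 = 22.5 (match) and 163.8 × 77,805 / 159,705 = 79.8 (training). The denominator terms are 36.05 × 6,006 / 9,611 = 22.5 and 155.6 × 81,900 / 159,705 = 79.8. The ratio is 1.00, as it must be when both risks are identical.

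**The case against.** The strongest reply is that the plan nowhere commits the group comparisons to pooled hours. Section 2.3.9 provides match-only and training-only rates. Seasons are explicitly examined by match, training or both. Study One has an objective on training versus match exposure (2.3.2), and 2.3.5.3 records the two exposures separately. The all-injury rate is tied to comparison with earlier studies, which is close to a descriptive role. Appendix J may name the rate to be compared. All of this stands, so the defect is that the between-group sentence is silent on the rate and on session type, not that pooling is stated.

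The size is also open to challenge. No injury rate or training volume is in the documents, the upper figures need a match rate ten times the training rate, and 2.3.4 and 2.4.4 describe a second division with fewer resources and less support, so equal training is not a given. That stands too. It makes the direction and size uncertain, but it does not remove the problem: the ratio stays at 1 only if match and training rates are equal, or if training hours happen to scale with match load.

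A reader might also infer that match-only and training-only rates are to be divided by match plus training time, because the formula mentions total exposure time. The natural reading is the total time of the exposure type concerned. A clearer sentence is worthwhile, but this is not evidence of a wrong denominator.

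**Conclusion.** The point holds for the comparison of divisions. The between-group rate ratio has no adjustment for session type and does not name its rate, and the all-injury rate defined beside it is pooled. With identical match and training risks, equal training hours per player, 11.5 second-division matches and a match rate 3 to 10 times the training rate, the crude division ratio is about 1.03 to 1.19, with one-season rejection of about 6% to 70%. The ratio is null at about 1.6 times more first-division training and falls below 1 beyond that. The rejection figures ignore clustering within teams and players.

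Two wider readings are tempting and not supported. One is that the trial's arm comparison is distorted: randomised teams share one division, no systematic imbalance in match share is expected, and the extreme case gives 1.01 to 1.04. The other is that the season comparison is distorted: no difference in match share between seasons is shown, and the plan already lists match and training there. Nor do the documents show that the division with more matches per month must have the higher pooled rate.

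The change should be made because it improves the estimate at almost no cost. It does not call the randomised comparison into question.

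**What to change.** In 2.3.9, state that match injuries are divided by match hours and training injuries by training hours. State that the all-injury ratio between divisions is a Mantel-Haenszel rate ratio stratified by match/training, or the group term from a Poisson model with a match/training term and log hours as offset. Use the same estimator for the arms, for consistency, so that the cross-reference in 2.4.8 carries it over. Keep the pooled rate as a descriptive figure for comparison with earlier studies. If Appendix J already specifies this, bring 2.3.9 into line with it.

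The cost is a few sentences. The two kinds of hours are already collected separately under 2.3.5.3, and the match and training rates already planned require the setting of each injury to be known.

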### **2.3.2 Objectives**

- a. To determine the difference in etiology, nature, severity and location of injuries between first and second division soccer players
- b. To assess whether there is any relationship between injury pattern and players' age, playing position and division of play.
- c. To assess if there is any difference in injury pattern according to training and match exposure
- d. To describe the availability of the medical support into the teams

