### **2.3.3 Study design**

A prospective cohort study design will be used to follow up players for a period of two consecutive seasons.

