#### **2.4.2.1 Objectives**

- a. To assess if there is any difference in the occurrence of injuries before and after the introduction of the injury prevention warm up programme
- b. To assess if the compliance of the injury prevention warm up programme will be associated with the reduction injuries.
- c. To determine if there are any differences in injury incidence and exposure time between groups or over time

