Coaches will also be trained on first aid. During the training, they will receive the first aid course for two days that will be provided by the trainer from the Rwanda Red Cross. Questionnaires will be distributed to the coaches to assess their knowledge immediately after first aid training. At the end of season two (June 2016) questionnaires will be distributed to the coaches from both divisions to assess the knowledge retained after one year of intervention.

Coaches and medical personnel from the first division will be requested to continue the recording of injuries and exposure using the procedure they used in the season one (2014-2015). To increase compliance and proper recording, coaches will be visited at team practice by the researcher to see if proper implementation is occurring and additional instructions on the correct conduct of the exercises will be provided where necessary. Data collection during season two (2015-2016) will be the same as season one where players exposure time, occurrence of injuries, treatment will be assessed.

Figure 3: Study two framework

[figure not shown]

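### Section 2.3.9 assigns ANOVA to the two-season injury comparison and names no term for the teams and players that supply both seasons

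*Combined protocol and SAP*

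**What the plan says.** Study One is a cohort whose design is to "follow up players for a period of two consecutive seasons" (2.3.3). Section 2.4.7.1 adds: "Data collection during season two (2015-2016) will be the same as season one". For the comparison of seasons, 2.3.9 says: "The variations of injuries during match, training or both for the two seasons will be analyzed using Analysis of Variance (ANOVA". Its next sentence gives ANOVA also to playing position and division of play, which are between-group factors. The section then assigns z-statistics and rate ratios to between-group incidence, sets one significance level ("The level of significance for all the tests is set to 0.05") and refers to Appendix J for the details.

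Two further objectives are affected. Study One has "To assess if there is any difference in injury pattern according to training and match exposure" (2.3.2, objective c; listed as objective d in 1.3). Study Two has "To assess if there is any difference in the occurrence of injuries before and after the introduction of the injury prevention warm up programme" (2.4.2.1, objective a), and its objective c adds differences over time. For injury incidence in Study Two, 2.4.8 says only: "Analysis of the incidence of injuries comparing the two study groups and the two divisions will be done as explained in the study one".

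**The concern.** An independent-groups ANOVA treats the season-one and season-two observations as coming from unrelated units. Here they mostly do not. Two teams move each way between the divisions (2.3.6.1), so up to 19 − 2 = 17 second-division teams, and 33 − 4 = 29 teams overall, are in the same division in both seasons. Stable team features, such as pitch, playing style and the person recording injuries, affect both seasons and cancel in a within-team comparison. If they are left in the error term, the standard error is wrong.

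At stake is whether a change between seasons is missed for an avoidable reason or declared too readily. Change over time is also a Study Two objective, and 2.3.9 is the only available text that says how two seasons are compared. Match and training exposure also come from the same players, so wherever those are contrasted the same question arises. The z-statistics and rate ratios in 2.3.9 name no pairing either.

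**Working it through.** The plan gives no power, effect size, SD or correlation for this comparison, so there is no figure to reproduce. The sample size in 2.4.4.3 is for intervention against control.

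**A. One rate per team.**

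From the documents: 17 retained second-division teams (above) and alpha 0.05, taken as two-sided. Assumed: a difference d = 0.7 between-team SD (a 20% lower rate if the between-team coefficient of variation is about 0.29, since 0.20/0.29 ≈ 0.7) and a between-season correlation ρ from 0 to 0.7.

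- The unpaired test takes the variance of the mean difference as 2/n (SD units). The true variance is 2(1 − ρ)/n.
- The paired test's noncentrality is d√n / √(2(1 − ρ)), on n − 1 = 16 degrees of freedom. The unpaired test uses 2n − 2 = 32.
- The large-sample actual level of the unpaired test is 2Φ(−1.96/√(1 − ρ)).

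| ρ | Paired noncentrality | Paired power | Unpaired power | Actual level of unpaired test |
|---|---|---|---|---|
| 0 | 0.7√17/√2 = 2.04 | 48% | 51% | 5% |
| 0.3 | 2.44 | 63% | 51% | 1.9% |
| 0.5 | 2.89 | 77% | 51% | 0.6% |
| 0.7 | 3.73 | 94% | 52% | 0.03% |

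The powers come from simulation with 40,000 runs per setting; the noncentral t distribution gives the same paired values. At ρ = 0.5 the simulated level with 17 teams is about 0.8%. The difference in power therefore runs from 3 points in favour of the unpaired test (ρ = 0) to 12, 26 and 42 points against it.

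Player turnover weakens the pairing. If a share w of players carries over, the effective correlation is roughly wρ. For example, 0.7 × 0.5 = 0.35, at which a paired test with 80% power loses about 12 to 19 points when run unpaired.

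**B. One record per player and season.**

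Assumed: 17 teams of 30 players (30 is the registration maximum in 2.3.4), with variance shares of 5% for team, 10% for player, τ for team-by-season, and the remainder e = 0.85 − τ.

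- The independent-groups test takes the variance of the season difference as 2/(17 × 30).
- Team and player terms cancel between seasons, so the true variance is 2[τ/17 + e/(17 × 30)].
- The ratio of true to assumed variance is R = e + 30τ, and the actual level is 2Φ(−1.96/√R).

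| τ | R | Actual level |
|---|---|---|
| 0% | 0.85 | 3.4% |
| 2% | 0.83 + 0.60 = 1.43 | 10% |
| 5% | 0.80 + 1.50 = 2.30 | 20% |

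Simulation agrees (about 3%, 10% and 20%). In the middle row the between-season correlation of team means is (0.05 + 0.10/30) / (0.05 + 0.10/30 + 0.02 + 0.83/30) = 0.53. A correlation near 0.5 thus goes with a level under 1% in analysis A and about 10% in analysis B. The unit of analysis decides the direction.

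**C. Fit to Study Two.**

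Analysis A applies the change to every team. Only the intervention arm receives the programme (2.4.9). With 9 of 17 teams changing and ρ = 0.5, pooled before-after power is 9% unpaired and 26% paired. Within one arm of 9 teams it is 23% and 46%.

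**The case against.** ANOVA includes repeated-measures forms, and 2.3.9 does not say that an independent-groups form is meant. The details are referred to Appendix J, which was not available, so it cannot be said that the plan as a whole omits the pairing. This stands. What can be said is that 2.3.9 does not state it, and that extending ANOVA to position and division makes the ordinary form the natural reading.

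A reader might infer that the plan loses about a quarter of its power. That figure needs a correlation of about 0.5, which the documents do not give. A reader might also infer that the test is bound to be conservative. Analysis B shows the opposite is possible, and 2.3.9 does not name the unit; playing position, a player-level factor, is given to the same method.

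That match versus training is tested by this ANOVA is only one reading. The sentence more naturally makes season the factor and match, training or total injuries the outcomes. Likewise, 2.4.8 carries over the group and division comparisons only, so it does not assign ANOVA to the before-after comparison; it leaves that comparison without a named method.

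Finally, pairing is partial. Teams recruit between seasons and mid-season, and 2.4.4.1 and 2.4.7.1 allow teams to leave or join, so 17 and 29 are upper bounds. This reduces any loss but does not remove the link through the team.

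**Conclusion.** The point holds in a limited form. Section 2.3.9 assigns ANOVA to a comparison of two seasons supplied largely by the same teams and players, and does not say how the repeated observations are handled. If the analysis is run on independent groups, its standard errors are wrong.

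Neither the size nor the direction of the error is established. On team rates, the range is from no loss at correlation 0 to 42 points at 0.7 (17 teams, 0.7 SD). On player records, the actual level runs from about 3% to 20% under the assumed variance shares. The correlation, effect size and variance shares are all assumptions. The conclusion is also conditional on Appendix J: if it already specifies a repeated-measures or mixed analysis, only the wording of 2.3.9 needs to change.

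**What to change.** In 2.3.9, name the unit of analysis. Replace plain ANOVA for the season contrast, and for match versus training where that is tested, with a Poisson or negative binomial model for injury counts. Use log exposure hours as offset, season and session type as fixed effects, and a random effect for team. If players are the unit, add random effects for team-by-season and for player; without the team-by-season term the problem in analysis B remains. Keep teams and players seen in only one season. A paired or repeated-measures analysis of team rates is the simple alternative.

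In 2.4.8, state that the before-after and over-time injury comparisons (2.4.2.1, objectives a and c) use the same model with a group-by-season term, because only the intervention arm receives the programme.

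The cost is a wording change and a slightly more complex model. No new data are needed, provided that team and player codes are kept across seasons; 2.3.8 assigns player codes but does not say that they persist, so this should be stated. Error degrees of freedom fall (16 against 32 with 17 teams), which costs a little power only if the correlation is near zero: 48% against 51% in the example.
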